Clinical events, such as VT/VF and sudden death, and cardiovascular events, for each group will be reported as percentages of the total population and annual frequencies per person‐year. Additionally, we will utilize the Kaplan–Meier method to calculate the cumulative event rates of clinical events, particularly focusing on VT/VF and sudden death, in the ICD/CRT‐D group, the non‐ICD (no device/CRT‐P) group among patients eligible for primary prevention, and compared these two groups using the log‐rank test. We will conduct Cox proportional hazards analysis to estimate hazard ratios (HRs) and 95% confidence intervals (CIs) for factors related to clinical events. Since the cardiovascular event rate is expected to provide sufficient data for multivariate analysis, we will conduct multivariate analysis to calculate the HR and 95% CI of the non‐ICD (no device/CRT‐P) group relative to the ICD/CRT‐D group in primary prevention for cardiovascular events by adjusting for clinically relevant factors. Based on the HINODE study, the annual occurrence rate of appropriate therapy for VT/VF with heart devices was approximately 6%. The all‐cause mortality rate for the group that did not have an ICD implanted (non‐device and pacing cohorts) was in the range of 8% (over the entire observation period).^17^ In the MADIT‐RIT Trial, the rate of appropriate ICD operation was also above 6%.^24^ In the MADIT II Trial, the rate of sudden cardiac death was approximately 10% in the non‐ICD group and less than 4% in the implanted ICD group, respectively.^15^, ^25^ Considering the low incidence of VT/VF and sudden death in primary prevention (approximately 5%–10%), the limited number of events may render multivariate Cox proportional hazards analysis impractical. Therefore, the propensity score model will be developed using selected variables according to clinical relevance. We will again draw the Kaplan–Meier method along with HR and 95% CI for VT/VF and sudden death for the propensity matched non‐ICD patient group compared with the propensity matched ICD patient group in primary prevention. As such, the results of elected patients after propensity score matching, along with all cohorts, along will be presented in the main text. For other groups, like those eligible for secondary prevention ICD and WCD, we plan to conduct the most comprehensive adjustment analysis possible, considering that the adjustable variables may change with the increasing number of cases.

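### Kaplan-Meier is the planned estimator of cumulative event rates, so absolute risk is overstated for every endpoint that a death outside it can preclude; the excess is small to moderate

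*Protocol article*

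**What the plan says.** The Statistical analysis section (2.6) names both the estimator and the quantity it estimates: "we will utilize the Kaplan–Meier method to calculate the cumulative event rates of clinical events, particularly focusing on VT/VF and sudden death". The groups are ICD/CRT-D and non-ICD (no device or CRT-P) among patients eligible for primary prevention, and the plan "compared these two groups using the log‐rank test". After propensity matching, "We will again draw the Kaplan–Meier method along with HR and 95% CI for VT/VF and sudden death", and the matched results are to go in the main text. Separately, event counts "will be reported as percentages of the total population and annual frequencies per person‐year".

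Table 3 lists, as clinical events, VT/VF and shocks, deaths by cause, heart failure hospitalization, stroke, myocardial infarction and bleeding. Table 4 makes these secondary endpoints, singly or in composites. Item 1 there joins VT/VF with sudden death. Item 3 is a cardiovascular composite that includes cardiovascular death. All-cause death is item 2.

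The article mentions neither competing risks nor a cumulative incidence function.

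**The concern.** A patient who dies of a cause outside the endpoint can no longer have the event. Kaplan-Meier removes that patient as if follow-up had simply ended, and spreads the remaining probability over survivors. One minus Kaplan-Meier then describes a hypothetical population in which nobody dies of anything else. It is not the share of patients who will have the event.

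Which deaths compete depends on the endpoint:

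- VT/VF and sudden death (item 1): non-sudden deaths only, since sudden death is an event.
- Cardiovascular composite (item 3): non-cardiovascular deaths only.
- Purely non-fatal endpoints such as heart failure hospitalization: every death, including sudden death.
- Cardiovascular death (item 10) and other causes of death (item 11): each competes with the other.
- All-cause death (item 2): nothing competes, and Kaplan-Meier is right.

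The Discussion says the registry should inform patient selection. The absolute risk of eligible patients, with and without a device, is a figure that readers will take from it, and the planned estimator biases it upward.

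**Working it through.** **Inputs from the document**

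- Event rate: "the annual occurrence rate of appropriate therapy for VT/VF with heart devices was approximately 6" per cent. I take h = 0.06 per year as a constant hazard and use it as a stand-in for item 1.
- Mortality without an ICD: it "was in the range of 8% (over the entire observation period"). This is all-cause, so it includes sudden deaths that count as events in item 1, and as a figure for competing death it errs high. The length of that observation period is not given.
- Horizon: enrolment opens April 2023 and follow-up closes December 2025, so t is at most 2.75 years.

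**Assumptions.** Hazards are constant. Competing death has hazard c, for which the document gives no direct value, so I show a range: 8% in total over 2.75 years, then 5%, 8% and 15% per year.

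**Formulas**

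- One minus Kaplan-Meier estimates 1 − exp(−h·t).
- True cumulative incidence is h/(h + c) × [1 − exp(−(h + c)·t)].

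**Calculation at t = 2.75 years**

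Kaplan-Meier: 1 − exp(−0.06 × 2.75) = 1 − 0.8479 = 15.2%, whatever c is.

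For 8% over the whole 2.75 years, c = −ln(0.92)/2.75 = 0.0303. Cumulative incidence is 0.06/0.0903 × [1 − exp(−0.0903 × 2.75)] = 0.664 × 0.220 = 14.6%.

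For c = 0.08: 0.06/0.14 × (1 − 0.6805) = 13.7%. For c = 0.15: 0.06/0.21 × (1 − 0.5613) = 12.5%.

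| Competing death | Kaplan-Meier | Cumulative incidence | Excess (points) | Relative |
|---|---|---|---|---|
| 8% over 2.75 years | 15.2% | 14.6% | 0.6 | 4% |
| 5% per year (assumed) | 15.2% | 14.2% | 1.0 | 7% |
| 8% per year (assumed) | 15.2% | 13.7% | 1.5 | 11% |
| 15% per year (assumed) | 15.2% | 12.5% | 2.7 | 21% |

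The excess grows with time. At 2 years, Kaplan-Meier gives 11.3% against 10.8%, 10.5% and 9.8% for 5%, 8% and 15% per year. At 1 year with c = 0.0303, the excess is about 0.1 point (5.8% against 5.7%).

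**Does the excess differ between device groups?** It depends on what is assumed. With h = 0.06 in both groups and c = 0.04 (ICD) against 0.08 (non-ICD), the 2.75-year excess is 0.8 against 1.5 points. With the same competing hazards but h = 0.10 (ICD) against 0.03 (non-ICD), as might happen if devices detect more VT/VF, the order reverses: 1.2 against 0.8 points.

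**Additivity.** Let S1 and S2 be the Kaplan-Meier curves for cardiovascular and other death, with all-cause survival S1 × S2. Then (1 − S1) + (1 − S2) exceeds 1 − S1·S2 by (1 − S1)(1 − S2), which is above zero once both kinds of death have occurred. If items 10 and 11 are both reported this way, they sum to more than item 2.

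**The case against.** The best defence is that the bias is small on the document's own figures and touches little that matters. The 8% is mortality over an entire observation period, not per year, and it includes sudden deaths. The exclusions (NYHA class IV, life expectancy below 12 months) should also hold competing mortality down. Only the first patients enrolled reach 2.75 years; with uniform accrual over 1.75 years, mean follow-up is about (2.75 + 1)/2 = 1.9 years. With about 325 patients per group (half of 651, and fewer in primary prevention), a 15% estimate has a 95% interval of about ±1.96 × √(0.15 × 0.85/325) = ±3.9 points, wider than any excess in the table. The endpoints concerned are secondary. All this stands and limits the severity. It does not make the estimator right: the bias has a known direction, and more patients would not shrink it.

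The planned person-year rates do not carry this bias. They, and the crude percentages, do not give risk at a stated time when follow-up varies, so they do not replace a correct cumulative curve.

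A reader might infer that the overstatement is worst in the non-ICD group because those patients are sicker. The document does not support that. It gives no competing mortality by device group and does not call that group sicker. The Introduction links under-use to ageing among other factors, without any mortality figures. The cited sudden-death figures of about 10% against less than 4% concern deaths that are events in item 1, not competing deaths. Nor does anything in the document show that non-sudden death is as frequent as VT/VF and sudden death.

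**Conclusion.** The point holds for absolute cumulative rates of secondary endpoints. Following the text as written would overstate them for every endpoint that some other death can preclude, both before and after matching. For item 1 at 2.75 years the excess is about 0.6 points (4% relative) on the reading closest to the document's mortality figure. It is about 1.5 to 2.7 points (11% to 21% relative) if competing death is 8% to 15% per year, rates that are assumptions and not in the document. These results rest on constant hazards and on the 6% per year rate of device therapy standing in for item 1. An unequal excess between groups is possible, but its presence and direction are open.

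The log-rank test and the Cox hazard ratios remain valid as cause-specific comparisons. All-cause death and the primary endpoint, the device implantation rate, are unaffected.

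**What to change.** In section 2.6, replace Kaplan-Meier by the Aalen-Johansen cumulative incidence for every endpoint except all-cause death, treating death outside the endpoint as the competing event. State which deaths compete: non-sudden death for VT/VF and sudden death, non-cardiovascular death for the cardiovascular composite, and any death for purely non-fatal endpoints. Apply this in the full primary-prevention groups and in the matched sample. Keep Kaplan-Meier for all-cause death. Keep the log-rank test and Cox models, and label them as cause-specific comparisons. Gray's test may be added but is not needed.

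The cost is a change of wording and a little more analysis work. Table 3 already collects event dates and causes of death, although deaths must be classed as sudden or not. Published event rates will be slightly lower.

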Date of informed consent Age, gender, height, weight Smoking habits: Current/Former/Never Alcohol consumption: Daily / 2–3 times a week/Never Underlying heart disease (Ischemic cardiomyopathy/non‐ischemic cardiomyopathy [Dilated cardiomyopathy/hypertrophic cardiomyopathy/hypertensive heart disease/others]) NYHA functional classification (I/II/III/IV) Medical history (Diabetes, hypertension, dyslipidemia, ischemic heart disease [History of myocardial infarction/Angina], history of heart failure, chronic obstructive pulmonary disease, history of stroke, peripheral arterial disease) Clinical Frailty Scale: 1–9 Medication History ① Beta‐Blockers: Yes/No ② ACEi/ARB (angiotensin‐converting enzyme inhibitor / angiotensin receptor blocker): Yes/No ③ Mineralocorticoid Receptor Antagonists: Yes/No ④ ARNi (Angiotensin Receptor‐Neprilysin Inhibitor): Yes/No ⑤ SGLT2i (Sodium‐Glucose Cotransporter 2 Inhibitors): Yes/No ⑥ Ivabradine: Yes/No ⑦ Pimobendan: Yes/No ⑧ Digoxin Preparations: Yes/No ⑨ Antiarrhythmics: Sodium Channel Blockers (Procainamide/Disopyramide/Flecainide/Cibenzoline/ Pirmenol/Aprindine/Propafenone), Potassium Channel Blockers (Amiodarone/Sotalol/Bepridil) ⑩ Anticoagulants: Warfarin/Direct Oral Anticoagulants (DOACs) ⑪ Antiplatelet Agents: Yes/No ⑫ Lipid‐Lowering Medications: Yes/No ⑬ Diabetes Medications (excluding SGLT2i): Yes/No History of revascularization (percutaneous coronary intervention, coronary artery bypass grafting) Presence of atrial fibrillation/flutter (paroxysmal/persistent/permanent) Presence of NSVT (≥5 beats) History of ablation therapy for NSVT/VT History of cancer (gastrointestinal/lung/other) Dialysis (yes/no) Echocardiogram (LVEDV [mL], LVESV [mL], LVDd [mm], LVDs [mm], LAD [mm], LVEF [%], presence of moderate or severe valvular disease [MR, TR, AR, AS]) Electrocardiogram (heart rate, rhythm, QRS duration [ms], presence of ventricular pacing) Laboratory data (NTproBNP [pg/mL] or BNP [pg/mL], WBC [×10^9^/L], lymphocyte count [×10^9^/L], Hb [g/dL], Plt [×10^9^/L], BUN [mg/dL], Cr [mg/dL], eGFR [mL/min/1.73 m^2^], UA [mg/dL], AST [U/L], ALT [U/L], rGTP [U/L], Tcho [mg/dL], Na [mmol/L], K [mmol/L], TP [g/dL], Alb [g/dL], CRP [mg/dL]) Confirmation of performance only Signal‐averaged electrocardiogram (present/absent) Holter monitoring (present/absent) Cardiac MRI (present/absent)
(2) At 12 Months (±3 Months) (WCD indication group: at 3 Months corresponding to the time of WCD removal phase and 12 months after removal phase)

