Device introduction For a case who are decided to receive no device implantation: Reasons for no introduction: (1) Patient does not want risk associated with implantation. (2) Patient does not believe in benefit of ICD/CRT‐D/WCD. (3) Patient unable to pay for device. (4) Other reasons. For a case of introduction: Date of device implantation, indication for device implantation (primary prevention / secondary prevention), type of device and product name (WCD/ICD/CRT‐P/CRT‐D/other), (new implantation/upgrading) For a WCD case, the date of removal Invasive treatments during follow‐up Date of invasive treatment, type of invasive treatment (implantable cardiac device/implantable loop recorder/catheter ablation/revascularization/device reoperation) Clinical event investigation Event Date ① Presence of VT (five or more consecutive beats), VF, and/or shock events (including inappropriate shocks) ② Presence of death (cardiovascular death, other causes of death: specify details) ③ Hospitalization due to heart failure ④ Other cardiovascular events requiring hospitalization ⑤ Stroke/TIA and systemic embolism ⑥ Myocardial infarction, unstable angina ⑦ Major bleeding (ISTH criteria) ⑧ Clinically significant bleeding

Abbreviations: CRT‐D, cardiac resynchronization therapy defibrillator; CRT‐P, cardiac resynchronization therapy pacemaker; ICD, implantable cardioverter defibrillator; ISTH, International Society on Thrombosis and Haemostasis; TIA, transient ischemic attack; VT, ventricular tachycardia; VF, ventricular fibrillation; WCD, wearable cardioverter defibrillator.

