### Primary and secondary endpoints

2.4

The primary endpoint is the rate of cardiac implantable electronic device implementation. The secondary endpoints are shown in Table 4. Other significant factors besides the primary endpoint include the incidence of VT/VF, the presence of sudden death, all‐cause mortality, and HF hospitalization, as well as other variables. We will gather standard clinical background information, each patient's Clinical Frailty Scale score, laboratory test results (including measures of nutritional status), and serial changes, which will also serve as secondary endpoints.

**TABLE 4 joa313028-tbl-0004:** Primary and secondary endpoints.

Primary endpoint	
Rate of cardiac electronic device implantation (ICD, CRT‐D, WCD, CRT‐P, or None)	
Secondary endpoints	
Occurrence of any of the following	
1. VT/VF and Sudden death^a^	
2. Death from any cause	
3. Cardiovascular events (stroke/TIA or systemic embolism, myocardial infarction/unstable angina, cardiovascular death [including sudden cardiac death], hospitalization for heart failure, or other cardiovascular event requiring hospitalization)	
4. Stroke/TIA or systemic embolism	5. Myocardial infarction/unstable angina
6. Heart failure requiring hospitalization or other cardiovascular event requiring hospitalization	
7. Major bleeding (ISTH criteria^b^)	8. Clinically significant bleeding
9. Major bleeding or clinically significant bleeding	10. Cardiovascular death
11. Other causes of death	12. Device‐related complications
13. Invasive cardiac interventions (surgery, catheter‐based treatments, pacemaker implantation, etc.)	
14. If patients refused implantation, reasons for ICD/CRT‐D/WCD implantation refusal (1. Patient does not want risk associated with implantation, 2. Patient does not believe in benefit of ICD/CRT‐D/WCD, 3 Patient unable to pay for device, or 4 Other reasons)	
Change in the following from the time of enrollment to 1 year (WCD cases: at the time of WCD removal and 12 months after removal):	
1. NYHA (New York Heart Association) functional classification, Clinical Frailty Scale	
2. Echocardiographic measures	
3. Hemoglobin, hematocrit, creatinine, NT‐proBNP or BNP	
4. Nutritional status markers (serum albumin concentration, white blood cell count [peripheral blood lymphocyte count], total cholesterol, C‐reactive protein)	

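### VT/VF is detected differently with and without an ICD, so the planned comparison of VT/VF and sudden death is biased downward and may mask or reverse an ICD benefit

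*Protocol article*

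**What the plan says.** Secondary endpoint 1 in Table 4 is "VT/VF and Sudden death". Section 2.6 gives it the most attention among the clinical events. Kaplan–Meier curves are to show "cumulative event rates of clinical events, particularly focusing on VT/VF and sudden death", for ICD/CRT-D and for the non-ICD "group among patients eligible for primary prevention, and compared these two groups using the log‐rank test". Because few events are expected, a propensity-score analysis follows, giving "HR and 95% CI for VT/VF and sudden death for the propensity matched" non-ICD group relative to the matched ICD group. Matched and whole-cohort results are both meant for the main text.

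The event item collected is in Table 3: "Presence of VT (five or more consecutive beats), VF, and/or shock events (including inappropriate shocks"). It sets no requirement for symptoms, duration or treatment. Table 4 does not say whether inappropriate shocks enter endpoint 1.

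On rhythm recording, Table 1 schedules an ECG at registration and 12 months for patients with an ICD indication. For those with a WCD indication it schedules ECGs at registration, at 3 months and 12 months after the removal phase. Ambulatory monitoring appears only at registration in Table 2, under tests noted as done or not: "Holter monitoring (present/absent"). No ambulatory monitoring is scheduled during follow-up.

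The limitations paragraph of the Discussion names patient bias and confounding. It does not mention detection.

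**The concern.** The exposure being compared is also the main instrument for measuring part of the outcome. A short, symptomless run of VT can be counted in an ICD/CRT-D carrier and will mostly go unseen in a patient with no device. ICD shocks, appropriate or not, can occur only in carriers. Within the non-ICD group, CRT-P carriers and patients given a loop recorder (an item in Table 3) fall somewhere between the two.

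A propensity score balances patients at baseline and does nothing about how events are found afterwards. A larger sample does not shrink the bias either.

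The Discussion wants the results applied to patient selection for ICDs in Japan. If non-implanted patients appear to have few arrhythmic events partly because nobody was recording, the comparison misleads on exactly that question.

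**Working it through.** **Is there a plan figure to reproduce?** No. The article states no HR, power or detection rate for this comparison, and the target of 651 patients is a feasibility number. The check is therefore a bias calculation.

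**Inputs**
- VT/VF rate λ = 6% a year. Section 2.6 says that "the annual occurrence rate of appropriate therapy for VT/VF with heart devices was approximately 6" per cent. This is device-delivered therapy only, so it is narrower than Table 3's five-beat definition.
- Sudden death: section 2.6 cites about 10% without and under 4% with an ICD, with no time base. I take these as annual, then as two-year figures (5% and 2% a year, an assumption). I add two assumed lower settings: 1% in both groups, and 2.5% versus 1%.
- d, the share of VT/VF detected without an ICD: not in the article. Assumed 0.10–0.50.
- Simplifications: constant rates, the same true VT/VF rate in both groups, full detection with an ICD, and no inappropriate shocks.

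**Formulas** (non-ICD versus ICD)

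Observed HR = (λ·d + S_non) / (λ + S_ICD)

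True HR = (λ + S_non) / (λ + S_ICD)

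The observed HR equals 1 at d* = 1 − (S_non − S_ICD)/λ.

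For VT/VF alone the observed HR is simply d, so 0.10–0.50 when the truth is 1.

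**Combined endpoint, λ = 6%**

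| Sudden death per year, non-ICD / ICD | True HR | Observed, d = 0.10 | Observed, d = 0.50 | d* |
|---|---|---|---|---|
| 1% / 1% | 0.07/0.07 = 1.00 | 0.016/0.07 = 0.23 | 0.040/0.07 = 0.57 | 1.00 |
| 2.5% / 1% | 0.085/0.07 = 1.21 | 0.031/0.07 = 0.44 | 0.055/0.07 = 0.79 | 0.75 |
| 5% / 2% | 0.11/0.08 = 1.38 | 0.056/0.08 = 0.70 | 0.080/0.08 = 1.00 | 0.50 |
| 10% / 4% | 0.16/0.10 = 1.60 | 0.106/0.10 = 1.06 | 0.130/0.10 = 1.30 | 0 |

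The observed HR lies below the true one in every row. It falls below 1 only when d is less than d*. In the last row that never happens.

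**Effect of the five-beat definition.** If it raised λ to an assumed 20%, then with 10% versus 4% and d = 0.25 the observed HR is (0.05 + 0.10)/(0.20 + 0.04) = 0.625, against a true 0.30/0.24 = 1.25. The wider the definition, the heavier the part of the endpoint that depends on detection.

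**The case against.** The strongest reply is that the endpoint also contains sudden death. That needs no recorder and is expected to run against the non-ICD group. This stands. A reader might infer that the HR measures nothing but detection, or that the analysis is bound to make forgoing an ICD look protective. The article does not support either reading: with its own 10% versus 4% taken as annual, the HR stays above 1 across the assumed range of d.

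A reader might also expect a statistically significant false result. That depends on chosen inputs. Take 150 matched pairs, d = 0.25, sudden death 1% in both groups and a mean follow-up of 1.88 years. That gives 282 person-years per group, 19.7 versus 7.1 events, z = −2.35 and p about 0.02. The 1.88 years assumes even accrual, whereas section 2.5 reports delayed enrolment and sites added later. At the guaranteed one year the same inputs give 10.5 versus 3.8 events, z = −1.71 and p about 0.09. No p-value should be attached to this point.

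It would also be too absolute to say that the comparator has no rhythm recorder, given CRT-P and loop recorders. Nor does the article say what device memory stores, so complete capture with an ICD is an assumption.

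Finally, the reach is limited. The primary endpoint is the implantation rate. The planned multivariable HR is for cardiovascular events, and that composite in Table 4 does not list VT/VF. The Discussion already says that the study cannot establish cause and effect. That caveat concerns causation and confounding, and it does not tell a reader that the outcome was measured unequally.

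**Conclusion.** The point holds as a directional bias in one prominent secondary comparison. VT/VF is ascertained according to device status, so its contribution to the non-ICD versus ICD HR is too low, and propensity matching cannot repair it. In the settings tabulated, a true HR of 1.00 appears as 0.23–0.57, 1.21 as 0.44–0.79, and 1.60 as 1.06–1.30.

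These sizes rest on an assumed d of 0.10–0.50, a VT/VF rate of 6% a year that is equal in both groups, and sudden-death rates that are either assumed or given in the article without a time base. The downward direction needs only d below the detection share with an ICD. Whether a benefit is merely masked or actually reversed cannot be settled from the article. The comparison should be fixed before analysis. The primary endpoint and the rest of the plan are not undermined.

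**What to change.** In section 2.6, base the between-group log-rank test and the matched HR on sudden death and on all-cause death. Sudden death is defined in the footnote to Table 4 and all-cause death is already endpoint 2, so neither needs a new outcome or a rhythm recorder.

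Report VT/VF and shocks as rates within ICD/CRT-D and, separately, within non-ICD patients, without a test between them.

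If a VT/VF comparison is kept:
- label it secondary;
- exclude inappropriate shocks and short symptomless runs known only from device memory;
- state how episodes ended by an ICD are counted. Restricting to clinically overt VT/VF is not symmetric by itself: an episode stopped by the ICD before arrest, syncope or admission would drop out, while the same episode without an ICD would count.

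Add differential detection to the limitations paragraph.

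The wording change is small, but the loss of events is real. With sudden death at 2.5% versus 1% and d = 0.25, 100 person-years per group yield 2.5 + 1 = 3.5 sudden deaths. The mixed endpoint would yield (1.5 + 2.5) + (6 + 1) = 11 events. Intervals for sudden death will be wide. All-cause death should supply more events: section 2.6 cites mortality of around 8%, over the whole observation period, in patients without an ICD.

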### Study schedule

2.3

Patients diagnosed as eligible for ICD or WCD indications will start enrollment in this study when informed consent regarding their medical condition and treatment options is obtained. All items at the time of enrollment and follow‐up in both of patient groups eligible for ICD and WCD indications, are listed in Tables 1 and 2. The brief items include age, gender, height, weight, dairy habits, underlying heart disease, NYHA functional classification, medical history, Clinical Frailty Scale,^22^ medication history including HF treatment, the presence of atrial fibrillation/flutter or NSVT, history of revascularization or ablation for NSVT/VT, history of cancer, hemodialysis, echocardiographic parameters, simple electrocardiogram information, and laboratory data. For patient eligible for ICD indications, follow‐up items including laboratory data, echocardiographic and electrocardiographic parameters, NYHA classifications, Clinical Frailty Scale scores, and HF medications will also be collected again at 12 months after enrollment. For patients eligible for WCD indications, we will collect these follow‐up items at 3 months after enrollment, and again at 12 months thereafter. Simultaneously, we will monitor the observation items for at least 1 year, and until the final follow‐up period in cases followed up beyond 1 year, as in Tables 1 and 3. These include device introduction information, invasive treatments, and the occurrence of clinical events. After the observation period ending in December 2025, we will organize and analyze the data comprehensively by March 2026. Results of the study will be published in one or more peer‐reviewed journals by June 2026.

**TABLE 1 joa313028-tbl-0001:** Study schedule and main observation items.

Patient eligible for the indication of an ICD (including CRT‐D) Item(s) recorded		Registration	At 12 months after registration*	Final follow‐up
Patient information	Age, sex, height, weight, lifestyle habits, comorbidities, etc.	●		
	Electrocardiogram Echocardiogram	●	●	
	NYHA functional classification, Clinical Frailty Scale	●	●	
	Laboratory test results, medication information	●	●	
Observation items	Device implantation date (If not implanted, provide reason)			
	Invasive cardiac interventions			
	Clinical events (VT, VF, hospitalization for heart failure, cardiovascular death, etc.)			

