NYHA functional classification (I / II / III / IV) Echocardiogram (LVEDV [mL], LVESV [mL], LVDd [mm], LVDs [mm], LAD [mm], LVEF [%], presence of moderate or severe valvular disease [MR, TR, AR, AS]) Electrocardiogram (heart rate, rhythm, QRS duration [ms], presence of ventricular pacing) Labotatory data (NTproBNP [pg/mL] or BNP [pg/mL], WBC [×10^9^/L], lymphocyte count [×10^9^/L], Hb [g/dL], Plt [×10^9^/L], BUN [mg/dL], Cr [mg/dL], eGFR [mL/min/1.73 m^2^], UA [mg/dL], AST [U/L], ALT [U/L], rGTP [U/L], Tcho [mg/dL], Na [mmol/L], K [mmol/L], TP [g/dL], Alb [g/dL], CRP [mg/dL])

Abbreviations: AR, aortic regurgitation; AS, aortic stenosis; Alb, albumin; ALT, alanine aminotransferase; AST, aspartate aminotransferase; BNP, brain natriuretic peptide; BUN, blood urea nitrogen; CRP, C‐reactive protein; Cr, creatinine; eGFR, estimated glomerular filtration rate; Hb, hemoglobin; LAD, left atrial diameter; LVDd, left ventricular diastolic diameter; LVDs, left ventricular systolic diameter; LVEF, left ventricular ejection fraction; LVEDV, left ventricular end‐diastolic volume; LVESV, left ventricular end‐systolic volume; end‐systolic volume; MR, mitral regurgitation; NT‐proBNP, N‐terminal pro‐brain natriuretic peptide; NSVT, Non‐sustained ventricular tachycardia; NYHA, New York Heart Association; Plt, platelet; rGTP, γ‐glutamyltranspeptidase; Tcho, total cholesterol; TP, total protein; TR, tricuspid regurgitation; UA, uric acid; VT, ventricular tachycardia; WBC, white cell count.

**TABLE 3 joa313028-tbl-0003:** Observation items.

Observation Items (To be observed for a minimum of 12 months from the date of registration)

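### ICD/CRT-D and non-ICD are compared as fixed groups although implantation comes after registration, and no time zero, landmark or time-dependent exposure is stated, so the outcome comparison is open to immortal-time bias

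*Protocol article*

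**What the plan says.** **Entry.** Under Study schedule (2.3), eligible patients "will start enrollment in this study when informed consent regarding their medical condition and treatment options is obtained". For a new implant, registration therefore comes before the device.

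**Clock.** The heading of Table 3 sets the observation items: "To be observed for a minimum of 12 months from the date of registration".

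**Exposure.** Device status is learned during follow-up. Section 2.3 says of the items monitored there: "These include device introduction information, invasive treatments, and the occurrence of clinical events". Table 3 lists, for patients who receive a device, "Date of device implantation, indication for device implantation".

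**Comparison.** Statistical analysis (2.6) names an ICD/CRT-D group and a non-ICD group (no device or CRT-P) and plans:
- Kaplan-Meier curves for the ICD/CRT-D group and the non-ICD "group among patients eligible for primary prevention, and compared these two groups using the log‐rank test";
- an adjusted Cox model giving the hazard ratio of non-ICD relative to ICD/CRT-D for cardiovascular events;
- Kaplan-Meier curves and a hazard ratio for VT/VF and sudden death "for the propensity matched non‐ICD patient group compared with the propensity matched ICD patient group in primary prevention".

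**WCD route.** Section 2.6 also says that patients who enter under the WCD criteria are classified as eligible for a primary-prevention ICD only at 3 months after registration.

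The article does not say when group membership is fixed, where the survival clock starts, or how an event before implantation is counted.

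**The concern.** Group membership depends on something that happens after the clock starts. Two errors follow, in opposite directions.

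- **Death.** A patient must live until implantation to count as ICD/CRT-D. The wait is then credited to that group as event-free time, and anyone who dies waiting counts as non-ICD. The device looks protective even if it does nothing.
- **Non-fatal VT/VF.** A patient who has VT/VF without a device and is then implanted brings that event into the ICD/CRT-D group. The device looks harmful.

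Propensity matching balances variables measured at registration. It cannot correct a group label that depends on later survival or later events.

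The comparison of outcomes with and without a device is purpose (2) in the Introduction and is repeated as an objective in the Discussion. Section 2.6 expects VT/VF or sudden death in only about 5% to 10% of primary-prevention patients. That is at most 33 to 65 events even if all 651 patients counted (0.05 × 651 = 32.6; 0.10 × 651 = 65.1), so a few misassigned events matter. The main outcome combines VT/VF with sudden death, so the net direction of the two errors cannot be predicted.

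**Working it through.** The plan gives no figure of its own on this point, so the check asks what the stated comparison would show if the device had no effect.

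**Inputs from the article**
- Follow-up F: enrolment from 1 April 2023 to 31 December 2024, with final follow-up by 31 December 2025, gives 1 to 2.75 years. Taken as uniform (assumption), the mean is (1 + 2.75)/2 = 1.875 years.
- Share implanted p = 0.5, from the 50/50 split under Sample size (2.5). That split covers all device types, so its use for ICD/CRT-D is an assumption.

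**Inputs assumed**
- Delay from registration to implantation: exponential with mean μ. The article gives no delay, so a range is shown.
- Death hazard λ: constant. The ratio hardly depends on it.

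**Approximation for death, fixed groups, clock from registration.** With d = μ/1.875:
- ICD group: the wait adds person-time but no deaths, so its apparent rate is about λ(1 − d).
- Non-ICD group: it takes on the deaths during the wait, so its apparent rate is about λ(1 + d·p/(1 − p)), which is λ(1 + d) at p = 0.5.
- Non-ICD versus ICD rate ratio ≈ (1 + d)/(1 − d).

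| Mean delay | d | (1 + d)/(1 − d) | Simulation |
|---|---|---|---|
| 0.25 month (about a week) | 0.0111 | 1.02 | about 1.02 |
| 1 month | 0.0444 | 1.09 | about 1.10 |
| 2 months | 0.0889 | 1.20 | about 1.20 |
| 3 months | 0.1333 | 1.31 | about 1.32 |
| 6 months | 0.2667 | 1.73 | about 1.60 |

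The approximation overshoots at 6 months because some patients reach the end of follow-up before their implant. The simulated value is the one to use. Simulated ratios are nearly the same for hazards from 4% to 10% per year.

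**Alternative reading: ICD clock from implantation, non-ICD clock from registration.** The simulated ratios are 1.01, 1.05, 1.13 and 1.23 at 0.25, 1, 3 and 6 months. This is smaller but still biased: the non-ICD group keeps the deaths during the wait, while the waiting time of those later implanted belongs to neither group.

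**Time-dependent exposure.** Assigning each event and person-year to the device status at that moment returns 0.99 to 1.01 in every scenario.

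**Log-rank type I error for death.** With an assumed hazard of 4% per year and an assumed 390 primary-prevention patients, the rejection rate at a nominal 5% is about 5%, 7% and 11% at mean delays of 1, 2 and 3 months.

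**VT/VF, direction only.** At 6% per year with no device effect, suppose 30% of not-yet-implanted patients with VT/VF are then implanted and counted as ICD. The ICD versus non-ICD ratio becomes about 1.8. At 0% it stays at 1.0. The 30% is invented to show the mechanism; the article gives no such share.

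**The case against.** The strongest reply is that the article does not say patients are grouped by eventual receipt. It names two groups without an assignment rule or time origin, and a fuller plan might supply both. That is correct, and a reader who concludes that the article prescribes ever-implanted grouping goes beyond the text. What stands is that the article specifies fixed-group Kaplan-Meier, log-rank, Cox and matched analyses on an exposure that arises after registration. Both natural ways of carrying these out are biased.

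Second, enrolment happens at the treatment discussion, so the wait may be short. This also stands: at about a week the bias is negligible. Nothing in the article assures such a delay.

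Third, a reader might put the false-positive rate at 15% to 26%. Those values need a death hazard of 8% per year and all 651 patients, at delays of 2 and 3 months. The documents do not support either input. The 8% mortality quoted in section 2.6 is over a whole observation period, and the comparison is limited to primary prevention, while 651 also covers secondary-prevention and WCD patients.

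Fourth, Table 3 records the indication, so a patient implanted after VT/VF could be identified as secondary prevention. That helps to find such cases. Dropping them, however, removes an event from the non-ICD experience in which it occurred, so it does not repair the comparison. Many recorded VT episodes (five or more beats) may also prompt no implant, which is why no size is claimed for this error.

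Fifth, the 3-month classification of WCD-route patients is a usable starting point for that subgroup, but section 2.6 does not make it their time zero. The limitations in the Discussion mention confounding and incomplete control of bias, not timing.

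**Conclusion.** The concern holds in conditional form. The stated comparison uses fixed device groups, while device status is determined after registration, and no rule on timing is given. On the natural reading it favours the ICD/CRT-D group for death and can work against it for VT/VF.

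For death, the spurious non-ICD versus ICD ratio runs from about 1.02 at a one-week mean delay to about 1.60 at 6 months. This rests on assumed exponential delays, 50% implanted and uniform follow-up of 1 to 2.75 years. The effect on the log-rank test is modest under the assumed 4% per year and 390 patients, reaching about 11% at 3 months.

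Two wider inferences are not supported. The primary endpoint, the implantation rate, is untouched. The article also does not show that the bias will be large, since the delay is unknown. The point concerns the outcome comparison in purpose (2).

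**What to change.** In section 2.6:

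1. **State time zero.** Use registration, and for WCD-route patients the 3-month eligibility classification.
2. **Make the exposure time-dependent.** Count a patient as non-ICD until the recorded ICD/CRT-D implant date and as ICD/CRT-D from then on. Assign each event and person-year to the status at that moment, in the Cox models and in the rates per person-year. This also settles how events before implantation are counted. Alternatively, prespecify a landmark, fix device status at it, and analyse patients then alive and event-free.
3. **Align the matching in time.** Match each implanted patient to an eligible, event-free, not-yet-implanted patient at the same time since registration (risk-set matching), or match within the landmark cohort.
4. **Replace the fixed-group curves and log-rank test** with versions consistent with the choice in step 2.

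The cost is analysis wording only, because implant and event dates are already collected. A landmark analysis has the small downside of dropping early events.
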